## **15. FINANCE**

The trial is funded by the NIHR Health Technology Assessment Programme. The HTA programme is part of the National Institute for Health Research. It produces independent research information about the effectiveness, costs and broader impact of healthcare treatments and tests for those who plan, provide or receive care in the NHS.

The trial will be coordinated by the MRC CTU. A written agreement with the site Principal Investigator and/or the Investigator's institution and the MRC CTU will outline the funding arrangements to sites.

## 16. TRIAL COMMITTEES

### 16.1 Trial Management Group

A trial management group (TMG) that will include the MRC CTU trial physician and/or chief investigator, the trial statistician, the MRC trial manager and data manager will be formed to conduct the day-to-day management of the trial. A charter will be developed to describe the functioning of the TMG.

### 16.2 Trial Steering Committee

A Trial Steering Committee (TSC) will be formed to provide overall supervision for the trial. This will include an independent Chairman, two other independent clinicians, a community representative, the Chief Investigator, external clinical principal investigator and the trial statistician. A charter will be developed to describe the functioning of the TSC.

### 16.3 Independent Data Monitoring Committee

An Independent Data Monitoring Committee (IDMC) will be formed comprising two clinicians, a community representative, and a statistician, none of whom have direct involvement with the trial. The IDMC will report to the TSC. A charter will be developed to describe the functioning of the IDMC.

### 16.4 Endpoint Review Committee

An Endpoint Review Committee (ERC) will be formed to review the documentation relating to reported serious drug or disease-related clinical events, in order to ascertain whether these meet the criteria for this secondary endpoint. The ERC will consist of two clinicians, one of whom will not be directly involved with the trial.

**Figure 3: Diagram of relationships between trial committees**

[figure not shown]

## 17. PUBLICATION

It is anticipated that a number of opportunities will arise for publication during the course of, and following completion of this trial. In order to avoid disputes regarding authorship, it is important to establish a consensus approach that will provide a framework for all publications derived in full or in part from this clinical trial. The following approach is derived from the Lancet and from the publication policies used in OPTIMA and ESPRIT studies:

- All publications are to be approved by the TMG and TSC before submission for publication. The TMG and TSC will resolve problems of authorship and maintain the quality of publications.
- Trial findings will be submitted to journal(s) that support open access publication within the time frame specified by the MRC policy. All publications will acknowledge the HTA and any other appropriate funding sources.
- For all publications, the TSC will either nominate a chairperson or approve an individual's request to chair a manuscript writing committee. The chair will usually be the primary or senior author. The chairperson is responsible for identifying fellow authors and for determining with that group the order of authorship that will appear on the manuscript. The proposed writing committee will be submitted to the TSC for ratification prior to the first draft of the manuscript.
- The chairperson of any writing committee will also provide the TSC with a list of investigators to be presented in an appendix at the end of the paper. This list will include investigators who contributed to the investigation being reported but who are not members of the writing committee. In principle, substudy reports should include all investigators for the main study, although in some instances where a smaller number of investigators have made any form of contribution, it may be appropriate to abbreviate the listing. All headline authors in any publication arising from the main study or sub-studies must have made a significant academic/project management contribution to the work that is being presented. "Significant" must be defined by a written declaration of exactly what the contribution of any individual is believed to have been. In addition to fulfilling the criteria based on contribution, additional features that will be considered in selecting an authorship group will include the recruitment of patients who contributed data to any set of analyses contained in the manuscript, and /or the conduct of analyses (laboratory and statistical), leadership and coordination of the project in the absence of a clear academic contribution.
- The data derived from this clinical trial are considered the property of the MRC. The presentation or publication of any data collected by the participating investigators on patients entered into this trial is under the direct control of the TMG and TSC. This is true whether the publication or presentation is concerned directly with the results of the trial or is associated with the trial in some other way. However, although individual participating investigators will not have any inherent right to perform analyses or interpretations or to make public presentations or seek publication of any of the data other than under the auspices of and with the approval of the TMG and TSC, they will be encouraged to develop sub-studies or propose analyses subject to the approval by the TMG and TSC.
- Outcome data by treatment group will not be revealed to the participating investigators until the data collection phase of the trial has been completed. This policy safeguards against possible bias affecting the data collection. The IDMC will be monitoring the outcome results and may recommend that the trial be stopped for safety reasons or if a definitive answer is reached earlier than the scheduled end of the trial.

## 18. PIVOT EXTENSION

- Following the last trial visit, an extension phase will continue for up to a further 5 years in which basic treatment and clinical outcome data will continue to be collected by means of an annual retrospective review of the patients' case notes.

The following data will be collected annually:

- Changes in ART during the review period
- HIV viral load results during the review period
- Resistance test results during the review period
- Latest CD4 count and serum creatinine during the review period
- AIDS events, serious non-AIDS events or death during the review period

No reporting of serious adverse events will be required during this extension phase.

These parameters will be compared in an updated analysis of the primary endpoint and selected secondary endpoints, following the same approach as in the main trial analysis.

Consent for the extension phase will be taken at the patient's last trial visit

The Trial Steering Committee may decide to terminate the extension phase of the trial at any time before the end of the 5 year period, taking into account factors such as the scientific relevance of the data, proportion of patients retained in clinical follow up, and funding issues.

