**Secondary outcome measures:**

- Serious drug\* or disease-related complications
- Adverse events\*
- Virological rebound
- CD4+ count change
- Health-related Quality of Life change\*
- Neurocognitive function change\*
- Cardiovascular risk change\*
- Health care costs\*

\* = not evaluated during the extension phase

For more details refer to section 9.

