#### **7.1.8 Annual clinical notes review during the extension phase**

During the extension phase, the following data will be collected by annual retrospective review of the patients' routine clinic records:

- Changes in ART during the review period
- HIV viral load, latest CD4 count and creatinine results during the review period
- Resistance test results during the review period
- AIDS events, serious non-AIDS events or death during the review period

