## 7.2 Procedures for assessing efficacy

### 7.2.1 Viral load

VL testing will be performed at the local site laboratory with the standard assay for detecting low levels of VL that is routinely used at the site. The site laboratory will be required to demonstrate satisfactory participation in a recognised quality control program for VL testing.

For the purposes of statistical analysis and for clinical management in the PIVOT study protocol, confirmed VL rebound is defined as 3 consecutive VL tests  $\geq 50$  copies/ml, with at least 4 weeks between the first and last test. One of the 3 tests may be a repeat of the same sample.

The procedure for documenting confirmed VL rebound is as follows. Any VL result  $\geq 50$  copies/ml will be initially verified by re-testing the **VL rebound original sample** on a separate laboratory run. If it is not possible to re-test the original sample, the patient should be called for a repeat blood test within four weeks from the date of the original sample. The re-test on the original sample, or on the repeat blood draw taken within 4 weeks, are regarded as equivalent and are termed the **VL rebound original sample repeat test**. If the result of the original sample repeat test is confirmed as  $\geq 50$  copies/ml, the patient will be recalled for a **VL rebound confirmation sample** that must be taken at least four (and if possible less than 8 weeks) after the date of the original sample. If an original sample repeat test was not performed, then it is essential for the PIVOT protocol that a **VL rebound confirmation sample repeat test** be performed. This confirmation sample repeat test can be done either by retesting the confirmation sample on a separate laboratory run, or by recalling the patient for a repeat blood test as soon as possible (and within four weeks from the date of the confirmation sample).

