## 7.3 Procedures for assessing safety

A symptom evaluation and targeted physical examination will be performed at each visit.

Body composition changes will be evaluated at baseline, annual visits and the final study visit as follows:

- Waist circumference will be measured between the lower border of the ribs and the iliac crest, in a horizontal plane.
- Hip circumference will be measured at the widest point over the buttocks.
- Patients will be asked about any change in fat in the face, arms, legs or abdomen. Taking into account the patient's opinion, the research nurse or doctor will grade facial lipoatrophy as none, moderate (evident on inspection), or severe (immediately obvious).

Patients will be asked about symptoms of peripheral neuropathy at baseline, annual visits and the final study visit. A brief neuropathy examination will be performed at baseline and the final study visit in all patients, and at intervening annual study visits if the patient reports neuropathy symptoms

Cardiovascular risk factors will be assessed at annual trial visits, and risk will be quantified using the Joint British Societies cardiovascular risk prediction charts (see Appendix 11).

Blood will be drawn at trial visits to assess laboratory safety parameters according to standard-of-care as indicated in the schedule of trial assessments (see section 1.3). Additional safety blood tests or investigations will be performed to investigate symptoms or monitor emergent laboratory test abnormalities as clinically indicated.

All adverse events will be reported on the case report form. Adverse events (clinical and laboratory) will be graded using the 2004 Division of AIDS toxicity grading scale (see Appendix 7). Serious adverse events will be defined according to the EU Directive 2001/20/EC Article 2 based on ICH GCP, and will be reported to the MRC CTU for the duration of the main trial i.e. whilst patients are attending trial visits according to standard timelines (see section 11).

Diagnostic criteria for selected serious AIDS and non-AIDS events are defined in the protocol (see section 9.2.2 and Appendices 8 and 9), and sites will be encouraged to investigate patients in a way that allows determination of whether patients meet the specified diagnostic criteria. An independent endpoint review committee will review these endpoints to ensure that they satisfy the criteria.

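### Section 18 applies the main-trial analysis to the extension without allowing for the change in how rebound and resistance are detected after the last trial visit

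*Combined protocol and SAP*

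**What the plan says.** **Main trial.** Viral load (VL) is tested every 12 weeks (sections 6.2.2 and 6.3.4), with extra early tests on monotherapy. A result of 50 copies/ml or more leads to a re-test and then, if verified, a recall visit at 4–8 weeks (7.1.6, 7.2.1). A genotype is required when the confirmation sample is also 50 or more, with central testing if local sequencing fails (7.2.3). For analysis, "confirmed VL rebound is defined as 3 consecutive VL tests" at or above 50 copies/ml, at least 4 weeks from first to last; one may be a repeat on the same sample.

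**Extension.** Section 18 says "an extension phase will continue for up to a further 5 years", with data taken from "an annual retrospective review of the patients' case notes". The items include "HIV viral load results during the review period" and "Resistance test results during the review period" (the latter also in 7.1.8). No testing interval, re-test, recall or genotype is required. The analysis is to be "an updated analysis of the primary endpoint and selected secondary endpoints, following the same approach as in the main trial analysis". Under 9.5.1 that approach is Kaplan-Meier and Cox.

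**Composite.** Section 1.1.5 marks the drug part of serious complications as "not evaluated during the extension phase". Sections 7.1.8 and 18 nevertheless collect serious non-AIDS events, and 9.2.2 lists severe facial lipoatrophy and severe peripheral neuropathy among these. Section 7.3 ties the first to trial visits ("Body composition changes will be evaluated at baseline, annual visits and the final study visit as follows") and sets the same timing for neuropathy symptoms. Section 18 does not name its selected secondary endpoints.

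**The concern.** One event definition is applied across two systems of detection. The primary endpoint is a resistance result, so time without a genotype can only count as event-free, whatever the virus is doing. The three-test rebound definition was written around the re-test and recall. If routine care takes two raised values and then changes the drugs, the third qualifying test may never be done.

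A fall in the observed rate after the last trial visit could then be read as a real fall in risk. If clinics monitor or genotype patients differently according to the regimen they know the patient is taking, the comparison between arms is distorted too. The composite has the same difficulty in plainer form: its content may change at the last trial visit, and the protocol does not say how.

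**Working it through.** **1. Inputs from section 9.3.** Uniform recruitment over 24 months, 60 months in total, 97% of controls event-free at 3 years, and a margin of 10 points over 3 years. These reproduce the main-trial sample size. The margin hazard ratio is ln(0.87)/ln(0.97) = 4.572. Freedman's formula at two-sided 5% and 85% power gives 21.85, so 22 events. The event probability at the control hazard is 0.03978, and 22/0.03978 = 553.01, hence 554. The match is without a visible allowance for loss. The extension has no stated sample size, event count or power to reproduce.

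**2. How much time is affected.** Follow-up in the main trial runs from 36 to 60 months, mean 4.0 years. A full 5-year extension would be 5/(4 + 5) = 56% of patient time; with 18-month recruitment (the upper end in 1.1.4) it is 5/(4.25 + 5) = 54%. These are upper figures, taking full re-consent, no losses and all five years. The share of patients still in the main trial at month t, between 36 and 60, is (60 − t)/24. That averages 75% in year 4 and 25% in year 5; it is 100% before and 0% after.

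**3. Testing frequency alone does little.** If an event persists, a longer interval delays detection by half the interval on average. The fraction of 5-year extension events still undetected at the end is about (interval/2)/5 years: 2.3% at 12-weekly, 4.6% at 24-weekly and 10% at 52-weekly testing. A material fall needs loss of the re-test, recall and genotype, or short episodes: an 8-week episode is caught with probability 8/12 = 0.67 at 12-weekly and 8/24 = 0.33 at 24-weekly testing.

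**4. Equal under-detection.** Let s be detection in the extension relative to the main trial. The documents give no value for s, so it is an assumption, as is the 3% monotherapy hazard; the 1% control hazard is close to the plan's −ln(0.97)/3 = 1.02% per year. Over 8 years the shares in step 2 give 3 + 0.75 + 0.25 = 4 years of main-trial time and 4 of extension time. Observed risk is 1 − exp(−h(4 + 4s)).

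| s | Control (h = 0.01) | Monotherapy (h = 0.03) | Difference (points) |
|---|---|---|---|
| 1 (true) | 7.7% | 21.3% | 13.6 |
| 0.7 | 6.6% | 18.5% | 11.9 |
| 0.5 | 5.8% | 16.5% | 10.6 |
| 0.3 | 5.1% | 14.4% | 9.4 |

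The same s multiplies both hazards, so the hazard ratio stays at 3 in each phase. With the plan's control hazard, a true hazard ratio of 2, and 4 years of main trial plus 5 of extension, the difference is 8.0 points at s = 1, 7.2 at 0.8, 6.0 at 0.5 and 4.9 at 0.25.

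**5. Unequal detection.** With both true hazards at 1% and s = 0.7 in one arm, 0.4 in the other, the 8-year risks differ by exp(−0.056) − exp(−0.068) = 1.1 points although the truth is zero. The hazard ratio within the extension would be 0.4/0.7 = 0.57 or its inverse, 1.75.

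**6. The three-year contrast.** Every patient has at least 36 months of planned main follow-up. The only leakage is among late recruits, whose final visit may fall up to 12 weeks before the closing date (schedule note 9). At a hazard ratio of 2 the 3-year difference is 2.9 points for every s.

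**7. The composite.** Section 9.2.2 does not divide its components into drug and disease parts, so the exclusion in 1.1.5 cannot be mapped to a list. Sections 7.1.8 and 18 then collect the undivided category. No assumption about detection is needed to see this.

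**The case against.** A reader might infer that event rates must fall in the extension by construction. The documents do not support that. Section 7.1 says trial assessments follow routine care closely, and 12.1.2 says visits keep to the usual frequency apart from two early tests on monotherapy. Section 18 collects all VL results in each period, so annual is the interval of abstraction, not of testing. Main-trial genotyping already uses the site's usual laboratory, and nothing says that clinics omit confirmation or genotyping. This stands: a fall is possible, not implied. But similar visit frequency does not show that routine care runs the re-test, recall and genotype sequence, and 7.1 lists rebound visits as additional.

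A reader might also infer that the extension tilts the trial towards declaring non-inferiority. The criterion is the difference over three years, and step 6 shows that this rests almost wholly on main-trial data. Nor does section 18 say that the updated analysis replaces the main conclusion; pooling both phases into one curve is a natural reading of an update, but it is not stated.

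On rebound, the three tests need not be on one regimen, so a value still raised after a switch can count, and 9.2.2 leaves alternative definitions to the SAP. On the composite, severe neuropathy as defined in Appendix 8 could be found in clinic notes. These points soften the examples but leave section 18 with no rule for the change in detection.

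**Conclusion.** The gap is real and worth closing, chiefly for the long-term estimates. Ascertainment changes at the last trial visit and section 18 carries the main-trial approach across it unadjusted. Equal under-detection would understate long-term risk differences where the arms truly differ, with the hazard ratio essentially intact; detection that differs by arm would bias both measures. The confirmatory three-year result is essentially untouched.

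The sizes are illustrations. They rest on assumed detection of 30–70%, an assumed monotherapy hazard, and a full extension with complete consent and no loss. Section 18 requires fresh consent and lets the steering committee stop early, so the affected share of time may be smaller. If routine care detects as well as the trial did, nothing is lost. The inconsistency in the composite holds whatever detection turns out to be.

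**What to change.** In section 18 and the SAP:

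1. State that the non-inferiority conclusion rests on main-trial time, censored at the last trial visit.
2. Report extension results by phase among consenting patients, either separately from the last trial visit or with phase as a time-updated factor. Show VL tests and genotypes per patient-year by arm. Use, for analysis only, a rebound definition that routine data can meet, for example two consecutive VLs of 50 copies/ml or more, and re-apply it to the main-trial data for comparison.
3. Name the selected secondary endpoints. Restrict any composite spanning both phases to components ascertained in both, and reconcile 1.1.5, 7.1.8, 9.2.2 and 18 accordingly.

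The cost is wording, plus a count of tests from data already being abstracted. The extension estimate will be less precise than a single pooled curve.

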APPENDIX 15: PROTOCOL VERSION 4.0 LISTING OF CHANGES  
APPENDIX 16: PATIENT INFORMATION SHEET – EXTENSION PHASE  
APPENDIX 17: CONSENT FORM – EXTENSION PHASE

## APPENDIX 3: GP LETTER

(To be presented on local-headed paper)

[Date]

**PIVOT:** Protease Inhibitor monotherapy Versus Ongoing Triple-therapy in the long-term management of HIV disease

EUDRACT: 2007-006448-23  
ISRCTN04857074

Dear Dr \_\_\_\_\_

Your patient, \_\_\_\_\_, has consented to participate in the trial named above and given permission to notify you of their participation in the trial. On \_\_\_\_\_ they were randomised to the \_\_\_\_\_ arm of the trial.

This is a randomised controlled clinical trial to compare a strategy of switching to boosted protease inhibitor (PI) monotherapy to continuing combination antiretroviral therapy (ART) for long-term management of HIV-infected patients.

This trial aims to determine whether a strategy of switching to PI monotherapy is non-inferior to continuing triple drug therapy in terms of the proportion of patients who maintain all their available drug treatment options after at least 3 years of follow-up.

Please find enclosed a copy of the patient information sheet for this trial and contraindicated medication.

You will be kept up-to-date with your patient's progress but if you have any concerns or questions regarding this study please contact the responsible doctor:

Dr \_\_\_\_\_ at \_\_\_\_\_(Hospital)

Tel: \_\_\_\_\_

Kind regards,

[Name]

[Position]

## APPENDIX 4: EQ-5D QUESTIONNAIRE

### Describing your own health today

By placing a tick in one box in each group below, please indicate which statements best describe your own health state today.

#### Mobility

- |                                       |                          |
|---------------------------------------|--------------------------|
| I have no problems in walking about   |  |
| I have some problems in walking about |  |
| I am confined to bed                  |  |

#### Self-Care

- |                                                 |                          |
|-------------------------------------------------|--------------------------|
| I have no problems with self-care               |  |
| I have some problems washing or dressing myself |  |
| I am unable to wash or dress myself             |  |

